### Interim analyses {21b}

Preliminary data analyses will occur over two quarters beginning at quarter 4 of year 2. The interim analysis will examine the number of cigarettes smoked per day per participant and the number of subjects who have stopped smoking.

### Methods for additional analyses (e.g., subgroup analyses) {20b}

As a supplemental set of analyses, we will examine the questionnaires and their ability to predict smoking cessation. The questionnaires will be used as originally designed such that psychometric data for each questionnaire will inform their scoring and interpretation.

### Methods in analysis to handle protocol non-adherence and any statistical methods to handle missing data {20c}

The primary analysis will use the intent-to-treat approach (ITT) which requires all randomized participants to be included in the statistical analysis and use the last value carried forward method to account for missing data, which tends to be conservative. Thus, if a patient only comes once, their smoking status and other characteristics will be that of baseline measurement and no change in the values with time will be noted.

### Plans to give access to the full protocol, participant-level data, and statistical code {31c}

We will provide the protocol, participant-level data, and statistical code upon request.

## Oversight and monitoring

### Composition of the coordinating center and trial steering committee {5d}

The research team will provide oversight for the conduct of the research study. The research team will record changes in policy that occur over the study period and that relate to the general care environment to LACDHS/DMH clinics. Additionally, the research team will record issues and barriers that arise over the study period as well as changes to workflow that the team makes during implementation. Periodic study team meetings will serve as the source of this information on implementation context, barriers, and changes. The DPH IRB and Department of Mental Health HSRC reviewed the protocol and consent and recommended changes that were incorporated into both. The IRB deemed that a data safety monitoring board was unnecessary as the study is low risk. Furthermore, the study is an implementation trial using already established treatments, and the primary aims are not assessing if treatment work but whether the treatments work in real-world contexts. Thus, a community advisory board was assembled composing of community members and staff members of the participating clinics served as the study’s independent steering committee.

### Composition of the data monitoring committee, its role, and reporting structure {21a}

Because the study has minimal risk, the DPH IRB and HSRC determine that no data safety monitoring board (DSMB) or data safety monitoring plan (DSMP) is needed.

### Adverse event reporting and harms {22}

Although the study has minimal risks and we do not expect any adverse events, we will notify the Department of Public Health (DPH) Institutional Review Board (IRB) and Department of Mental Health HSRC should they occur. During the consenting process, the study procedures will be explained to participants to help reduce any risks. The study coordinators will collect information from participants, including whether they are having an adverse experience with medications, but because the medication management is managed by the clinic and not as a research intervention, we direct participants to contact their prescribing clinicians and can facilitate patients making that connection. The only adverse events that would be collected as part of the study itself are related to the research procedures such as problems with the survey administration, CO testing, and urine testing. Collected data will not include adverse events with the care patients are receiving at the clinics. Albeit not collected, the most frequent adverse event of varenicline includes nausea (25%), of bupropion includes insomnia (12%), and of nicotine patch includes abnormal dreams (12%) [21].

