#### Primary aims

*Primary aim 1*: To test whether STUD participants have greater improvement in an objective measure of smoking behavior than TAU participants.

*Primary aim 2*: To test the penetrance of smoking cessation medications and counseling services in the STUDS arm vs. the TAU arm and between mental health and primary care clinics.

*Primary aim 3*: To test the dose effect on smoking cessation among those who receive medication and counseling services. Specifically, investigate if multiple medications plus counseling are more effective than single medication plus counseling, and what the dose-response effect of the number of counseling sessions on smoking abstinence.

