## Trial design {8}

The study design consists of a 5-year implementation, cluster-randomized comparative effectiveness trial comparing intervention clinics with TAU. Intervention clinics provide smoking cessation group counseling and medication management and are integrated into primary care and community mental health clinics. TAU offers information about the California Smoker’s Helpline and usual provider and clinician counseling. Participants in TAU will be asked at each data collection point (baseline, 3, 6, and 12 months) about any smoking cessation services received including prescribed and over-the-counter smoking cessation medication. Each clinical site in LACDHS is part of a cluster, and there will be a 5:1 ratio in the assignment of clinics assigned to the intervention as compared with the TAU. There are eighteen outpatient clinics participating in the study, eleven from LACDHS and seven from LACDMH (see the “Study setting {9}” section for full details of study sites). The present study aims to enroll 1000 participants from the clinics that will offer smoking cessation services and 200 from clinics not offering smoking cessation services. There are four data collection points, baseline, 3 months, 6 months, and 12 months. Each data collection point will take approximately 30–45 min. These interviews will take place at the participant’s primary care clinic or the site associated with where they usually obtain county-provided services.

In the first quarter of year 1, the research team will revise and prepare study material which will include the participant consent forms, participant and clinical staff questionnaires, recruitment documents, and any other related study material. In the second quarter of year 1, year 2, and the first quarter of year 3, the research team will support the implementation of smoking cessation services by providing training to the clinical staff at the intervention site. The research team will meet with the staff at the intervention sites in quarters 2 and 3 of year 1 and quarter 3 of year 2. The intervention will begin in quarter 2 of year 1 and continue through quarter 4 of year 3. The project may continue recruitment if funding remains available.

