#### Intervention description {11a}

Each clinical site in LACDHS is part of a cluster, and there will be a 5:1 ratio in the assignment of both LACDHS and LACDMH clinics assigned to the intervention as compared with TAU. The smoking cessation intervention will be a program embedded in the participating clinics and will include (1) a weekly 60–75-min CBT smoking cessation counseling group which will be led by facilitators that have been trained through the Kick Ash program and may be a nurse, pharmacist, clinician, SUD counselor, behavioral health clinician, or counselor and (2) smoking cessation medication that will be prescribed by a psychiatrist, pharmacist, or primary care doctor licensed clinician. Participants will be offered 6 weekly consecutive groups focusing on gaining necessary skills to aid in the decrease or total cessation of smoking behaviors. Those attending the groups will gain alternative coping strategies, relapse prevention strategies, and tools and resources to assist with reaching smoking cessation. Regarding the counseling group, participants will be able to repeat the groups willingly as needed until total smoking cessation is obtained. Smoking cessation medications will include varenicline (Chantix), bupropion (Zyban), nicotine patches, gum, and lozenges. Participants prescribed varenicline will be prescribed 0.5 mg of varenicline once daily for 3 days, then 0.5 mg twice daily for the next 4 days, then 1 mg twice daily thereafter. Those prescribed bupropion (Zyban) SR 150mg will be offered and, if accepted, prescribed once daily for 1 week, followed by bupropion SR 300 mg once daily thereafter. Participants prescribed NRT will be prescribed the standard prescription for nicotine NRT which includes a transdermal patch at a dose that approximates their current average mg of nicotine intake from tobacco products. Nicotine gums or lozenges (in either 2 mg or 4 mg strength) will also be offered and can be used as needed when experiencing cravings to smoke. TAU offers information about the California Smoker’s Helpline and usual provider and clinician counseling. Participants in TAU will be asked at each data collection point (baseline and 3, 6, and 12 months) about any smoking cessation services received including prescribed and over-the-counter smoking cessation medication.

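### Medication adverse events are kept out of the study data for a reason that conflicts with the randomized intervention, so the trial cannot report them by arm

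*Protocol article*

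**What the plan says.** Adverse event reporting and harms {22} first describes what research staff will learn: "The study coordinators will collect information from participants, including whether they are having an adverse experience with medications". Participants who report a problem are directed to their prescriber, "because the medication management is managed by the clinic and not as a research intervention".

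The section then limits what counts as study data: "The only adverse events that would be collected as part of the study itself are related to the research procedures", with survey administration, CO testing and urine testing as the examples. It adds: "Collected data will not include adverse events with the care patients are receiving at the clinics". In place of trial data it gives literature rates for the commonest event with each drug: 25% for varenicline, 12% for bupropion and 12% for the nicotine patch.

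Other sections treat medication as part of what is being tested. Trial design {8} says: "Intervention clinics provide smoking cessation group counseling and medication management and are integrated into primary care and community mental health clinics". Intervention description {11a} lists as its second component "smoking cessation medication that will be prescribed by a psychiatrist, pharmacist, or primary care doctor licensed clinician". Primary aim 3 is to "investigate if multiple medications plus counseling are more effective than single medication plus counseling".

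The harms section and the section on communicating amendments {25} both say that no adverse events are expected and that the ethics boards will be told if any occur.

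**The concern.** Medication counts as the intervention when benefit is measured and as outside care when harm is measured. A reader of the results will want both sides, because the Discussion says that the services will continue if they prove effective. With the present wording, the tolerability side of that judgement would rest on rates from the literature, although research staff in this trial hear about adverse experiences directly.

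The notification promise is also unclear. The harms section expects no adverse events, yet quotes rates of 12% to 25% for the drugs on offer. It does not say whether a medication event reported to a coordinator would be notified to the boards.

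**Working it through.** No plan figure is in dispute, so the check compares passages.

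1. **Is the information obtained?** Yes. The harms section says coordinators collect it from participants. It gives no schedule and does not say how the answer is recorded.

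2. **Does it enter the study data?** No. Two sentences in the same section exclude it: one restricts adverse events to research procedures, the other rules out events of clinic care.

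3. **Does the stated reason fit the design?** No. The reason is that medication management is not a research intervention. Trial design {8} and Intervention description {11a} both make it a component of the arm to which clinics are randomized. Primary aim 2 measures how far medication and counseling reach patients in each arm, and primary aim 3 compares medication regimens.

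4. **Could another source supply the data?** None that is described.
   - Clinic records reach the team as clinic-level aggregates about care processes (Data management {19}).
   - There is no data safety monitoring board or plan (section {21a}).
   - The anxiety (BAI), depression (BDI-II) and withdrawal (MNWS) scales are given at baseline, 3, 6 and 12 months (section {18a}) and are not limited to one arm. They allow a comparison of symptoms by arm, but they do not tie a symptom to a drug or record an event such as nausea.

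5. **What is left under the stated rule?** Three procedures are named: survey, CO test and urine test. Trial design {8} says that breath and urine testing were suspended in March 2020, that in-person visits are not expected to resume, and that 12 TAU and 69 intervention participants had completed testing.
   - 12 + 69 = 81 participants.
   - Planned enrollment is 1000 + 200 = 1200, and 81 / 1200 = 6.75%.
   - For nearly everyone else, survey administration is the only named source of a reportable event.

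**The case against.** The strongest reply is that this is a deliberate and explained choice. Coordinators ask in order to refer the participant to the prescriber, and the next sentences define what counts as study data. The steering committee section {5d} describes an implementation trial of established treatments, and both ethics bodies judged the risk minimal. A reader might infer that the harms section flatly contradicts itself. The ask-then-refer reading removes that literal contradiction, and I accept it. It does not remove the conflict between the reason given and the sections that define the intervention. Minimal risk explains the absence of a monitoring board. It does not explain leaving tolerability out of the results.

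The reply is also right that the gap is narrower than it may look. A reader might infer that every participant is asked at every contact and that the answers are thrown away. The text says only that information comes from participants, gives no schedule, and does not say what happens to the answers beyond their not being study data. A reader might also infer that the trial can report no harms at all. The BAI, BDI-II and MNWS comparisons, including within mental health clinics, show otherwise.

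Two practical objections stand. There is no blinding, and TAU clinics do not offer the medication program, so a table by arm will largely reflect exposure. Recruitment began in October 2019 and follow-up ends in June 2022 under a protocol version dated January 2021, so a field added now would miss earlier visits.

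**Conclusion.** The point holds as a minor one about reporting. The reason for excluding medication adverse events conflicts with the protocol's own definition of the intervention and with primary aim 3, and the passages must be reconciled. The consequence is specific: participant-reported medication adverse events cannot be reported by arm. Those adverse events that do count as study data come almost entirely from survey administration since March 2020.

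No count of unrecorded events can be given. It is tempting to multiply the quoted 12% to 25% by a number of users, but the protocol states no expected number of medication users and no split by drug. It also expects 50% of participants to drop out of the research assessments.

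The conclusion assumes that no fuller document records these answers as study data. It implies nothing about how side effects are managed clinically.

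**What to change.** Reconcile the harms section with Trial design {8}, Intervention description {11a} and primary aim 3, so that medication has one status throughout. Then:

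- Record the coordinators' answer as study data at the remaining 3-, 6- and 12-month interviews in both arms: yes or no, which drug, and free text. The item can be asked by telephone.
- Tabulate it descriptively by arm and by medication exposure, without formal testing. TAU participants are already asked at each interview about prescribed and over-the-counter cessation medication.
- State whether such reports fall under the promise to notify the ethics boards.
- State as a limitation that participants interviewed before the change lack these data.

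Clinical handling stays with the prescriber, as now.

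The cost is a short addition to the existing survey, one table, a little more data entry and an ethics notification. The data will be solicited, unblinded, incomplete and dependent on recall between interviews, and should be labelled so. If the field cannot be added in time, reconciling the text and stating the limitation still answer most of the point at almost no cost.

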### Frequency and plans for auditing trial conduct {23}

We do not envision the need for an audit. It is possible, the DPH IRB or the Department of Mental Health HSRC may audit our study.

### Plans for communicating important protocol amendments to relevant parties (e.g., trial participants, ethical committees) {25}

The study has minimal risks and explaining the study during the consenting process will help reduce the risks. We do not expect any adverse events, but we will notify the DPH IRB and HSRC should they occur.

### Dissemination plans {31a}

[name], our community engagement specialist, will help to ensure that the findings are communicated in the most appropriate way to the desired audiences. She will be available for presentations at professional and community forums, conferences, and workshops. Furthermore, the project team will disseminate information about the project itself and later our research findings at local and national conferences. We will extend our reach to students and other trainees in the health professions field so that future health professionals are aware of findings. Finally, we will publish our findings in peer-reviewed scientific publications and local community publications or other outlets in order that the community may learn of our study outcomes. [name] had such an article published in the Los Angeles Sentinel in January 2018 that highlighted TRDRP research being conducted in South Los Angeles. She co-authored a poster presentation regarding embedding community stakeholders in T1-T2 research teams which was presented at professional conferences.

## Discussion

Smoking cessation best practices include coordinated medication and behavioral treatments. Specifically, medication such as nicotine replacement therapy, bupropion, and varenicline have been proven to be effective in assisting with smoking cessation. However, our preliminary data found that only 21.3% of identified smokers received some sort of intervention in DHS and DMH clinics. For these reasons, the present 5-year implementation study will offer group counseling as well as medication for smoking cessation services delivered in LACDHS and LACDMH clinics compared to matched LAC-operated sites with treatment as usual.

The study represents a collaboration of three large departments within the Los Angeles County Health Agency that together treat the majority of Medi-Cal beneficiaries in Los Angeles County. Individuals served by the health departments within the Los Angeles County Agency are disproportionately affected by tobacco use disorder, leading to a significant treatment gap in these public-funded medical and mental health settings. Therefore, it is important to set up a comprehensive smoking cessation clinic in DMH and DHS clinics that will offer counseling as well as medication for smoking cessation, as the present study does. Understanding the effectiveness and feasibility of smoking cessation services delivered in LACDHS and LACDMH clinics in comparison to treatment as usual will be useful in evaluating future implementation and potentially bridging the treatment gap in these publicly funded medical and mental health settings.

Although there are strengths of the study, there are notable limitations. In response to the COVID-19 pandemic, the breathalyzer and urine testing were temporarily suspended in March 2020 and not anticipated resuming in-person visits. The CO breathalyzer and urinary cotinine test was originally going to be used to corroborate participants’ abstinence from smoking cigarettes for seven consecutive days and assess levels of nicotine in the body. Furthermore, the COVID-19 pandemic has required study staff to shift from in-person group visits to individual visits done by telephone and consenting shifted to be completed by mail. Although the COVID-19 pandemic has required adjustments, the integrity of the study has continued to be upheld.

The success of completing the study will provide information on the effectiveness of what smoking cessation services or combination of services are helpful to individuals seeking smoking cessation. In addition, the study findings will provide information to outpatient clinics on the feasibility and procedures on setting up smoking cessation services as part of core services. Most notably, the services are delivered by LACDHS and LACDMH clinicians in LAC-operated settings; therefore, if found effective, the services will continue after study completion.

## Trial status

Recruitment began on October 1, 2019. Recruitment and follow-up visits are set to end on June 3, 2022. The current protocol is version 7 created on January 16, 2021.

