## Statistical methods

### Statistical methods for primary and secondary outcomes {20a}

Final analyses will begin in year 4 at quarters 2 and 3. Data analysis will utilize an intention-to-treat (ITT) approach as the primary analysis. An additional set of analyses will use a per-protocol (PP) paradigm that will only use subjects who attend at least 3, out of four visits, including month 12. Descriptive statistics will include number, percent, and mode for categorical data (gender, race/ethnicity, site, LACDHS/LACDMH, number of visits). Continuous variables of clinical characteristics (number of cigarettes smoked, number of years smoked, Fagerstrom score) and Behavioral Measures Battery will be used to describe the study population. Non-normal distribution will be transformed to satisfy the normality assumption for the parametric statistical tests. Scale variables will be presented as min, max, and median. Graphical presentations (histograms, boxplots, and spaghetti plots) will be used to facilitate the visualization of data and the time trend of endpoints and baseline variables. All statistical analyses will be performed using SAS 9.2 and a *P*-value <0.05 will be considered statistically significant.

For model 1, we will perform an analysis of covariance with the baseline value (site, racial-ethnic group, number of visits, age, weight, smoking status, and survey scores) as the covariate and compare the value at the end of the study. To evaluate the change over time between the groups that incorporates all the measures collected over the timeframe of the study, then a two-way repeated measures analysis of variance model will be used. For model 2, a multiple logistic regression model would be built using independent variables such as treatment group and pre-determined baseline covariates (including study site). We posit that using a covariate-adjusted model to evaluate outcome provides a sensitivity analysis for the primary results of a simple comparison of the achievement of smoking cessation. For both models, the analyses will incorporate the cluster-randomized design into the model using an appropriately chosen variance-covariance structure (up to the use of an unspecified structure). In addition, the models will include a term for LACDHS versus LACDMH sites and their interaction with the intervention group.

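### A single closing date for recruitment and follow-up, read as written, rules out month 12 for anyone enrolled in the last year, and the analysis rules would carry earlier values into that visit

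*Protocol article*

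**What the plan says.** All references are to the protocol article.

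- **Trial status:** "Recruitment began on October 1, 2019", and then "Recruitment and follow-up visits are set to end on June 3, 2022". One date serves both activities.
- **Trial design {8}:** "There are four data collection points, baseline, 3 months, 6 months, and 12 months". Table 1 shows the same four visits for everyone. No shorter schedule for late enrolees is described. The same section leaves open that recruitment may go on if there is money for it.
- **Missing data {20c}:** the primary intention-to-treat analysis is to include everyone randomized and to "use the last value carried forward method to account for missing data, which tends to be conservative". It adds that "if a patient only comes once, their smoking status and other characteristics will be that of baseline measurement".
- **Statistical methods {20a}:** the per-protocol analyses will "only use subjects who attend at least 3, out of four visits, including month 12". Model 1 compares the arms on the end-of-study value.
- **Outcomes {12}:** the analysis is made at every follow-up time point against baseline, so month 12 is one of three.
- **Eligibility criteria {10}:** dropout means refusing further research assessments or being unreachable. Section {14} expects 50% dropout.

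**The concern.** A 12-month follow-up for all cannot be combined with a common end date for enrolment and visits. Whoever joins in the last year has a month-12 visit that falls after closure. That visit is absent because of the calendar, not because the person withdrew or was lost. It is therefore outside the protocol's definition of dropout, and the 50% allowance does not cover it.

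The protocol nevertheless fixes a general rule that would apply. Carry-forward would assign a month-12 smoking status according to how early the person enrolled:

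- Someone with baseline only is recorded as still smoking, because entry requires current smoking.
- Someone abstinent at month 3 or 6 is recorded as abstinent at month 12, with any relapse unseen. If early quitting is commoner in the intervention arm, as the sample size assumptions of 25% versus 5% abstinence would suggest, this second effect could favour that arm. The protocol's description of the method as conservative is then unsafe.

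The per-protocol set, meant to reflect attendance, would in part reflect enrolment date.

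**Working it through.** **Inputs.** Recruitment start 1 October 2019 and common end date 3 June 2022 (Trial status); visits at 0, 3, 6 and 12 months (Trial design {8}); target 1000 + 200 = 1200, 50% dropout, 14 and 3 sites, 25% versus 5% abstinence, intra-cluster correlation 0.05 (Sample size {14}). Accrual over time is not given, so uniform accrual is an assumption and a range follows.

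**The plan's own figure.** The protocol gives no count of participants affected. Its only related figure is power of 99.4%. Effective sizes are 1000 / [1 + (71.4 − 1) × 0.05] = 221.2 and 200 / [1 + (66.7 − 1) × 0.05] = 46.7. With unpooled variance, SE = √(0.25 × 0.75 / 221.2 + 0.05 × 0.95 / 46.7) = 0.0432, and power = Φ(0.20 / 0.0432 − 1.96) = 99.6%. With 500 and 100 after dropout it is 98.7%. Both are close to the stated figure, so this formula is used below.

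**Dates.** 1 October 2019 to 3 June 2022 is 976 days. Share without a possible visit = days after the last usable enrolment date / 976.

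| Visit | Last enrolment date that allows it | Days after it | Share, uniform accrual | Of 1200 |
|---|---|---|---|---|
| Month 3 | 3 March 2022 | 92 | 9.4% | 113 |
| Month 6 | 3 December 2021 | 182 | 18.6% | 224 |
| Month 12 | 3 June 2021 | 365 | 37.4% | 449 |

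**What carry-forward would use for the 449.** At most baseline: 113. At most month 3: 224 − 113 = 111. At most month 6: 449 − 224 = 225. So up to 111 + 225 = 336 could carry a post-baseline status into month 12. All 449 fall outside the per-protocol set.

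**Range.** If 10% of participants enrol in the last 12 months, 0.10 × 1200 = 120 are affected; if 50%, 600.

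**Observed month-12 outcomes.** This needs a further assumption, that the full 50% dropout applies by month 12 and is unrelated to enrolment date. Under uniform accrual the observed share is (1 − 0.374) × 0.5 = 31%. For 10% and 50% late enrolment it is 45% and 25%.

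**Power.** Using only participants with a possible month-12 visit under uniform accrual, power is 99.2% before dropout and 96.8% after 50% dropout. With 10% to 50% late enrolment, the figure after dropout runs from about 98% to 95%. As a bound only, suppose every absent month-12 value counted as smoking. Rates of 25% × 0.626 × 0.5 = 7.8% and 5% × 0.626 × 0.5 = 1.6% in the full sample give 68.6%, against 88.0% for dropout alone (12.5% versus 2.5%).

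**The case against.** The Trial status line is a one-sentence note. It may be shorthand for the end of all study activity, with enrolment closing earlier. It does not say that the last participant joins on 3 June 2022. That stands as a caution. But nothing in the article gives an earlier stop, so the dates need reconciling either way.

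Month 12 is not named as the only primary time point, and months 3 and 6 are much less affected. That also stands. Month 12 still carries weight through model 1 and the per-protocol definition.

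Treatment of visits that were never due could be left to an analysis plan, which is not shown. This carries less weight, because {20c} already states a general rule for missing data without exempting such visits. That the rule would apply to them is an inference, though a natural one.

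A reader might go further in four ways that the document does not support:

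- **That late enrolees are all fixed as smokers.** Only those with baseline alone are, about 9% under uniform accrual. The 68.6% power figure is therefore not what the stated rule implies.
- **That the arm comparison is biased by recruitment timing.** This would need the arms or clinics to recruit at different times, and the article does not show that.
- **That power is lost.** Among participants with a possible month-12 visit it stays high on the plan's own assumptions.
- **That the final analysis comes before late month-12 visits.** The article says "The intervention will begin in quarter 2 of year 1 and continue through quarter 4 of year 3" and "Final analyses will begin in year 4 at quarters 2 and 3", but maps no study year to a calendar date. If 1 October 2019 is assumed to lie in year 1, quarter 2, the analysis window would close by about April 2023, before a month-12 visit for someone enrolled on 3 June 2022. That is an assumption, and the point here does not depend on it.

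**Conclusion.** The concern holds in a limited form. The closing dates of enrolment and follow-up are not distinguished. As written, they make month 12 impossible for anyone enrolled after 3 June 2021. The stated rules would then give those people an unobserved month-12 status in the intention-to-treat analysis and remove them from the per-protocol set.

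The date conflict needs no assumption beyond reading the sentence literally. The size does: 449 of 1200 rests on uniform accrual, and 120 to 600 is the fair way to present it. The direction of any error is not determined. Carried-forward smoking dilutes the difference, while carried-forward early abstinence may inflate it.

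**What to change.** 1. In Trial status, give two dates: last enrolment and last follow-up visit. Reconcile them with the 12-month schedule and with the allowance for continued recruitment in Trial design {8}.
2. Amend {20a} and {20c} so that the month-12 analysis, both intention-to-treat and per-protocol, includes only participants enrolled at least 12 months before follow-up closes. Apply the same rule at months 3 and 6. This restricts the present requirement in {20c} that everyone randomized be analysed, so that text must change too. Selection is by enrolment date, not by outcome or attendance.
3. State in {20c} that values are not carried into visits that were never due.

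The cost is wording and a smaller month-12 set: about 751 instead of 1200 before dropout under uniform accrual (1200 − 449), and 600 to 1080 over the range shown. Extending telephone follow-up to about 3 June 2023 would keep late enrolees in the set if enrolment does run to 3 June 2022. It is optional, depends on funding, and would require the final analysis to follow it.
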